For each model size, we will systematically evaluate two distinct inference configurations defined by the temperature hyperparameter, which controls the randomness of model outputs. We will test a conservative configuration (temperature = 0.1) designed to prioritize consistency and clinical reliability by producing more deterministic responses, and a rather liberal configuration (temperature = 0.8). In the NLP literature the effects of temperature are well represented but systematic clinical applications have yet to be done to our knowledge. Accuracy in multiple choice question answering tasks show high consistency in temperature ranging between 0 and 1, but an expansion to other problem types is recommended (59). This strategic selection of hyperparameters reflects the clinical tension between reproducibility critical for diagnostic applications where consistency across assessments is paramount and the risk of highly inconsistent outcomes that could potentially lead to incorrect diagnoses and treatment recommendations. In addition, we apply top-p (nucleus) sampling with a cumulative probability threshold of 0.9 to each analysis. This setting restricts sampling to the smallest set of tokens whose cumulative probability mass is at least 0.9, balancing output diversity with coherence.

This yields a 2 × 2 factorial design with four experimental conditions: 1. GPT-OSS-120B with temperature 0.1, 2. GPT-OSS-120B with temperature 0.8, 3. GPT-OSS-20B with temperature 0.1, and 4. GPT-OSS-20B with temperature 0.8. We will evaluate each condition's performance on primary outcomes including general diagnostic classification accuracy and suicidality detection, severity score prediction (correlation with standardized clinical measures), and clinical utility metrics such as sensitivity, specificity, and positive/negative predictive values. All model versions, hyperparameters, and inference code will be fully documented and made available to ensure complete reproducibility.

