Tier 1: Unimodal Baseline Analysis. We will analyze each modality independently to establish baseline predictive performance before considering fusion. For the text modality, we will conduct two-way mixed-effects logistic regression with outcomes (diagnostic classification or severity degree) regressed on the fixed effects of model size and temperature, with random intercepts for participant and session. Effect sizes will be reported as odds ratios with 95% confidence intervals. For the acoustic modality, we will conduct mixed-effects linear regression using a reduced set of the most clinically relevant acoustic features selected *a priori* based on prior literature associations with depression and suicidality, including pitch variability, energy measures, MFCC and jitter as predictors of continuously scored clinical outcomes (e.g., severity scores from standardized rating scales) (60, 61).Tier 2: Factorial Interaction Analysis for 2 × 2 Design. For text-based predictions, we will formally test the 2 × 2 factorial design using mixed-effects ANOVA to partition variance according to main effects (model size, temperature) and their interaction. Specifically, we will model primary outcome (e.g., predicted depression severity) as a function of fixed effects for model size (GPT-OSS-120B vs. 20B), temperature (0.1 vs. 0.8), and their interaction (Model Size × Temperature), with random intercepts for participants and sessions to account for the hierarchical data structure. This approach allows us to determine whether inference strategy recommendations (conservative vs. liberal temperature) can be applied consistently across model sizes, or whether optimization differs by model choice. If a significant Model Size × Temperature interaction emerges, it would suggest that clinical deployment requires model-specific tuning. Conversely, absence of interaction would support unified recommendations applicable regardless of computational constraints. We will report partial eta-squared (*η*²p) effect sizes with 95% confidence intervals for each factorial term.Tier 3: Multimodal fusion and Late-Fusion Integration. To evaluate how textual and acoustic information combine for clinical prediction, we will employ a structured late-fusion approach. For each of the four 2 × 2 factorial conditions, we will generate separate predictions from the GPT-OSS models (text modality) and from a logistic regression model trained on acoustic features (acoustic modality). We will then integrate these predictions through weighted averaging, with weights determined via cross-validation (80% training, 20% held-out validation) on a stratified subset of sessions. This approach maintains interpretability—each modality's contribution can be quantified—and avoids the architectural complexity that would introduce uncontrolled hyperparameter flexibility incompatible with pre-registration.We will quantify multimodal benefit by comparing fusion performance (AUC, sensitivity/specificity at clinically relevant decision thresholds) against the best unimodal baseline. If fusion provides incremental improvement beyond single modalities, we will use mixed-effects logistic regression with interaction terms to test whether the fusion benefit depends on model size or temperature setting. This tests the hypothesis that acoustic information provides complementary information that enhances text-based predictions uniformly, or whether certain model configurations better leverage multimodal information.

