
Statistical rigor and assumptions testing. For all mixed-effects models, we will verify assumptions including normality of residuals (Shapiro–Wilk test on standardized residuals), homogeneity of variance (Levene's test), and absence of multicollinearity (variance inflation factors < 5 for predictors). Violations of normality or homogeneity will be addressed through appropriate transformations (e.g., Box-Cox for acoustic features) or robust variance estimation. Missing data will be handled via maximum likelihood estimation under a missing-at-random assumption, standard for mixed-effects models.

Multiple comparisons within the 2 × 2 factorial framework will be controlled via Bonferroni correction applied within each outcome domain (text-based prediction, acoustic baseline, fusion). We will test all fixed effects (model size main effect, temperature main effect, Model Size × Temperature interaction) at *α* = 0.05 (two-tailed). *post-hoc* comparisons between specific factorial cells (e.g., testing whether GPT-OSS-120B at temperature 0.8 outperforms GPT-OSS-20B at temperature 0.1) will be pre-specified and corrected for multiple comparisons.

This simplified, focused approach ensures that our study adheres to pre-registration principles, prevents *post-hoc* methodological flexibility, and provides a reproducible framework that other research groups can directly replicate or build upon.

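### Tier 2 reads any significant model-size by temperature interaction as pointing to model-specific tuning, but an interaction in which both models favour the same tested temperature does not support that reading

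*Protocol article*

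**What the plan says.** All of this is in the protocol article under Statistical methods for primary and secondary outcomes. Two model sizes (120B and 20B) are crossed with two temperatures (0.1 and 0.8): "This yields a 2 × 2 factorial design with four experimental conditions".

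Tier 2 states its question as "whether inference strategy recommendations (conservative vs. liberal temperature) can be applied consistently across model sizes, or whether optimization differs by model choice". It then gives one reading for each result of the interaction test. For a significant result: "If a significant Model Size × Temperature interaction emerges, it would suggest that clinical deployment requires model-specific tuning". For the opposite: "Conversely, absence of interaction would support unified recommendations applicable regardless of computational constraints". Neither reading carries a condition on the direction of the temperature effect within each model.

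The paragraphs on statistical rigor add: "We will test all fixed effects (model size main effect, temperature main effect, Model Size × Temperature interaction) at" a two-tailed level of 0.05, with Bonferroni correction within each outcome domain. They also promise cell comparisons: "comparisons between specific factorial cells (e.g., testing whether GPT-OSS-120B at temperature 0.8 outperforms GPT-OSS-20B at temperature 0.1) will be pre-specified". The single example changes model size and temperature together, and nothing ties these comparisons to the tuning conclusion.

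The example response for Tier 2 is the prediction itself: "we will model primary outcome (e.g., predicted depression severity) as a function of fixed effects for model size".

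**The concern.** With two models and two temperatures, the question is whether the same temperature is preferable for both. That depends on the sign of the 0.1 versus 0.8 effect within each model. The interaction contrast is the difference between those two effects and is blind to their signs. Effects of unequal size but the same sign give a true interaction and one common preferred setting.

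If the results are written up as Tier 2 describes, the report could say that each model needs its own setting when its own data favour one setting for both. That would be a wrong answer to the question Tier 2 was built for, in a part of the plan meant to inform deployment.

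**Working it through.** **1. The plan's own figure.** The plan gives no power figure for the interaction. Its only sample-size figure is n = 162 (Sample size section). An exact two-sided binomial test of 0.50 + 0.11 = 0.61 against 0.50, rejecting at 68 or fewer or 94 or more, gives alpha 0.0491726 and power 0.8046757, as stated. I use 162 below as the number of sessions.

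**2. What the test can and cannot see.** Let d₁ and d₂ be the losses in performance on moving from 0.1 to 0.8 for 120B and 20B.

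- Interaction: d₁ − d₂ ≠ 0.
- Different preferred settings: d₁ and d₂ have opposite signs.

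The first does not imply the second. A simulation shows this (162 sessions, paired contrasts, 20,000 runs, two-sided 0.05, assumed effects in within-session residual SD units):

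| d₁, d₂ | Difference | Interaction significant |
|---|---|---|
| 0.4, 0.9 (same sign) | 0.5 | 89% |
| −0.25, +0.25 (opposite) | 0.5 | 89% |
| 0.3, 0.7 (same sign) | 0.4 | 72% |
| −0.2, +0.2 (opposite) | 0.4 | 72% |

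The rejection rate depends only on the difference, so the test cannot separate the two cases.

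**3. Size on an accuracy scale.** All effects here are assumptions; the documents give none.

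- n = 162 sessions, treated as independent.
- 120B: 3.5% of sessions turn wrong at 0.8 and 2.5% turn right, so d₁ = 0.01.
- 20B: 3% turn right and (3% + loss) turn wrong, so d₂ is the loss.

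For each model, n × variance of d = (wrong + right) − (wrong − right)².

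For a 20B loss of 8 points: 120B gives 0.06 − 0.0001 = 0.0599 and 20B gives 0.14 − 0.0064 = 0.1336. SE of the interaction = √[(0.0599 + 0.1336)/162] = 0.0346. Ratio = 0.07/0.0346 = 2.03. The chance of exceeding ±1.96 is about 53%.

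| 20B loss (points) | Difference | SE | Ratio | Significant at 0.05: normal approximation | Simulated |
|---|---|---|---|---|---|
| 2 | 0.01 | 0.0293 | 0.34 | 6% | 7% |
| 3 | 0.02 | 0.0303 | 0.66 | 10% | 11% |
| 4 | 0.03 | 0.0313 | 0.96 | 16% | 17% |
| 5 | 0.04 | 0.0322 | 1.24 | 24% | 24% |
| 6 | 0.05 | 0.0330 | 1.52 | 33% | 33% |
| 8 | 0.07 | 0.0346 | 2.03 | 53% | 53% |
| 10 | 0.09 | 0.0360 | 2.50 | 71% | 72% |
| 12 | 0.11 | 0.0373 | 2.95 | 84% | 85% |

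In every row 0.1 is truly better for both models. If the Bonferroni correction is taken over the three factorial terms (0.05/3), the simulated rate is 2%, 4%, 7% and 12% for losses of 2, 3, 4 and 5 points, and 35% for 8 points.

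**4. Would a stricter test of direction do instead?** One candidate rule claims different settings only when both within-model intervals exclude zero in opposite directions. In the step 3 scenarios it makes that wrong claim in under 1% of trials. It also misses real reversals. With 3% background flips each way, a true +4/−4 point reversal is detected in 13% of trials, against 64% for the interaction test. For +5/−5 the figures are 25% and 79%.

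**5. Would observed signs alone do?** No. In step 3 the SE of d₁ is √(0.0599/162) = 0.0192, so a true 1-point loss shows the wrong sign with probability about Φ(−0.01/0.0192) = Φ(−0.52) ≈ 30%. The strength of evidence for each direction has to be reported.

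**The case against.** **The wording is soft.** Tier 2 says an interaction would suggest tuning; it is an interpretation, not a binding algorithm. That is fair and limits the severity. It is still the only reading given, in a plan that presents itself as closing off post-hoc flexibility.

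**The results will show the direction anyway.** Performance is to be evaluated in all four conditions, and the cell comparison quoted is only an example. A reader might infer that the plan excludes within-model contrasts. It does not say so, and a fuller analysis plan may list them. What stands is that the stated conclusion rests on the interaction alone.

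**Tuning may still be needed.** A reader might infer that a same-direction interaction proves no model-specific tuning is required. Two temperatures cannot show that, since the best untested values may differ. The point covers only the choice between 0.1 and 0.8.

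**The pattern is not predicted.** A reader might infer that the protocol itself leads one to expect a same-direction interaction. It does not. It reports "Accuracy in multiple choice question answering tasks show high consistency in temperature ranging between 0 and 1" and recommends extension to other problem types. It describes 0.1 in terms of consistency and forecasts no direction for accuracy. If accuracy were stable over that range, little interaction of any kind would be expected.

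**The illustration is not Tier 2 as written.** The example response is predicted severity, while the accuracy figures assume a right-or-wrong response. The illustration also ignores that up to five sessions may come from one patient. Both are true. The argument in step 2 of the working holds for any performance response; the percentages do not carry over.

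**Conclusion.** The concern holds in a limited form. Tier 2 asks which of two temperatures is preferable for each model and draws its conclusion from a test that does not address direction. A significant interaction with both models favouring the same setting would be read the wrong way.

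The size is uncertain. Under the stated assumptions the misleading result arises in about 7% of trials when the 20B loss is 2 points and about 85% when it is 12 points, at 0.05. Losses of 5 points or less give at most 24%. Quoting only the upper part of that range would overstate the problem. The 1-point loss for 120B was not varied, and independence of sessions is assumed.

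The sample size, the error rates and the comparison with the reference rating are untouched. This is an interpretive flaw that should be corrected; it does not threaten the study as a whole.

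**What to change.** Keep the interaction test. Add to the pre-specified cell comparisons the paired within-session contrast of 0.1 versus 0.8 for each model size. Compute it on a performance measure against the reference rating (error or accuracy, not the predicted score itself) and give confidence intervals. Then replace the two interpretive sentences in Tier 2 with three outcomes:

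- **Opposite directions and a significant interaction:** report a need for different settings, stating how well each direction is supported.
- **Both contrasts clearly favour the same temperature:** report a common preferred setting, and describe any interaction as a difference in temperature sensitivity.
- **Anything else:** report that the direction is unresolved. Do not default to a common recommendation.

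Limit the conclusion to the two temperatures tested.

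The cost is two more contrasts in the multiplicity correction, some rewording, and a less definite conclusion in some cases. No further data or model runs are needed.

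### Residual normality and Levene checks are ordered for all mixed models although two of the four are logistic, and the example remedy transforms predictors rather than the clinical score

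*Protocol article*

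**What the plan says.** All the text is in the protocol article, section Statistical methods for primary and secondary outcomes.

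- **Scope of the checks.** The paragraph on statistical rigor opens "For all mixed-effects models, we will verify assumptions including normality of residuals". The normality check is a "Shapiro–Wilk test on standardized residuals", and Levene's test is named for equal variance. No model type is exempted.
- **Remedy.** "Violations of normality or homogeneity will be addressed through appropriate transformations (e.g., Box-Cox for acoustic features) or robust variance estimation".
- **Logistic models.** Tier 1 analyses the text modality by "two-way mixed-effects logistic regression with outcomes" regressed on model size and temperature, and reports odds ratios. In Tier 3, if fusion improves on the single modalities, "we will use mixed-effects logistic regression with interaction terms to test whether the fusion benefit depends on model size or temperature setting".
- **Linear models.** The Tier 1 acoustic model is a mixed-effects linear regression in which acoustic features (pitch variability, energy, MFCC, jitter) predict continuous clinical scores. Tier 2 is a mixed-effects ANOVA.

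The section closes by claiming that the approach guards against changes of method after the fact.

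**The concern.** Given its fitted probability, the residual of a binary outcome can take only two values. It cannot be normal, and its variance is tied to its mean. A normality test on ordinary standardized residuals therefore reports a violation when nothing is wrong, and the plan says that violations will be dealt with. The analyst must then choose between a transformation and robust variance in response to a signal that carries no information.

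The one transformation named is also poorly aimed. Acoustic features do not enter the Tier 1 text model at all. In the Tier 1 acoustic model they are predictors, while the residuals under test belong to the clinical score. Box-Cox also needs positive values, which cepstral coefficients may not have, and the text does not say what happens then.

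At stake are needless or misdirected remedial steps, and some analyst discretion in a section that sets out to remove it. No main result is made invalid.

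**Working it through.** **The plan's own figure.** No stated figure is in dispute; the sample size only sets the scale of the check. It reproduces: an exact two-sided binomial test with n = 162, p0 = 0.5, p1 = 0.61, rejecting at 68 or fewer or 94 or more, gives alpha 0.0491726 and power 0.8046757. With four model-by-temperature conditions per session, 162 sessions give 162 × 4 = 648 rows, and the 200 planned interviews give 200 × 4 = 800.

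**Why normality cannot hold.** The Pearson residual is (y − p)/√[p(1 − p)]. At the article's expected accuracy, p = 0.892, √(0.892 × 0.108) = 0.310. The residual is 0.108/0.310 = 0.35 for a correct answer and −0.892/0.310 = −2.87 for a wrong one. Two values are not a normal distribution, however good the model.

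**Why Levene follows the proportions.** The raw residual variance is p(1 − p): 0.096 at p = 0.892 and 0.75 × 0.25 = 0.188 at p = 0.75, a ratio of about 1.9. With equal p in all cells the variances are equal. Pearson scaling makes the variance equal but not the mean absolute residual, 2√[p(1 − p)], which is 0.62 at p = 0.892 and 0.87 at p = 0.75. Levene's test works on absolute deviations.

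**Simulation of the stated checks on a correct logistic mixed model.** Inputs from the article: 162 or 200 sessions, four conditions, random intercepts for participant and session, test level 0.05. Assumptions: a binary correct/incorrect outcome, 3 sessions per participant, random-intercept SDs of 0.5 or 1.0, cell accuracies as shown, residuals taken from the true conditional probabilities, 300 runs per scenario.

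| Cell accuracies | Shapiro-Wilk rejects (Pearson or deviance) | Levene rejects (raw) | Levene rejects (Pearson) |
|---|---|---|---|
| equal (0.892, 0.75 or 0.60) | 100% | 0.3%–4.7% | 1.7%–5.3% |
| 0.892 / 0.87 / 0.85 / 0.80 | 100% | 38%–76% | 16%–25% |
| 0.892 / 0.892 / 0.75 / 0.75 | 100% | 96%–100% | 55%–85% |

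Shapiro-Wilk also rejected in 100% of runs with only 40 sessions. On randomized quantile residuals, both tests rejected in 2.3% to 7.3% of runs, close to the nominal 5%.

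**The remedies, in a linear model.** These simulations used n = 200, one skewed (log-normal) predictor and no random effects. Shapiro-Wilk rejection before and after Box-Cox on the predictor:

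- skewed errors, truly linear effect: 100% before, 100% after;
- normal errors, truly linear effect: 4.6% before, 19.6% after;
- normal errors, truly logarithmic effect: 97.1% before, 4.9% after.

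Transforming the predictor thus helps when the functional form is wrong. It does nothing for skewed errors, and it can spoil a linear effect that was right.

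For robust variance, with error spread growing with the predictor and no true effect (4,000 runs), the type I error was 50.2% with model-based variance and 8.4% with HC3.

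**The case against.** The strongest defence is that this is a condensed article. The kind of standardized residual is not spelled out, and if the full plan means randomized quantile residuals for the logistic models, the tests behave properly. Box-Cox is only an example under appropriate transformations, so nothing bars transforming the outcome. Robust variance is offered in the same sentence and is harmless, if unnecessary, in a correct logistic model. No bias or loss of coverage in a trial result has been shown.

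Much of this stands, and it limits the point. A reader might infer that both checks always fail in logistic models, that the remedies cannot work, or that features with negative values must be dropped. The documents do not support this:

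- Levene's test stays near or below its nominal level when accuracies are equal.
- Robust variance does address unequal variance.
- A predictor transformation can cure a wrong functional form.
- No rule removes features.

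The checks are also reasonable in kind for the acoustic regression and the ANOVA. Residual plots in place of tests, z-standardised predictors, or robust intervals whatever the checks show would be preferences, not corrections.

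The appeal to condensation does not remove the core. The article does not leave the scope of the normality check open: it states it for every mixed model, and two of those are logistic.

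**Conclusion.** The point holds as a minor one. A normality check is prescribed for two logistic models to which it does not apply. On ordinary standardized residuals it will flag a violation essentially every time (100% of runs in every scenario tried) and set off a remedy that is not needed. Levene's test is uninformative in those models because it mainly mirrors differences in the cell proportions, though it does not always reject. In the linear acoustic model the example transformation does not correct non-normal errors in the clinical score; the robust variance option remains valid for unequal variance.

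This rests on reading standardized residuals as Pearson or deviance residuals and on a binary outcome. Sessions per participant and random-intercept SDs are assumed, but the Shapiro-Wilk result did not change across the values tried. The remedy figures come from a simple linear model without clustering and show direction, not the size to expect in this study. The likely effect on conclusions is modest.

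**What to change.** Amend the assumptions paragraph as follows:

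1. Limit the normality and equal-variance checks to the linear mixed models (Tier 1 acoustic and Tier 2 ANOVA).
2. For the logistic mixed models (Tier 1 text and Tier 3 interaction), check fit with simulated or randomized quantile residuals and with calibration.
3. State that a transformation made because of residual violations is applied to the outcome score, and that a predictor is transformed only to correct functional form. Name a method that accepts negative values where cepstral coefficients are involved.
4. Make robust variance the default remedy, so that the choice is not left to the analyst once the checks are seen.

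The cost is a few sentences and possibly slightly wider intervals where robust variance is used. No change to data collection or sample size is needed.

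### Holm's step-down correction would give the same family-wise error control as the named Bonferroni correction and reject at least as much: a cheap improvement, not an error

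*Protocol article*

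**What the plan says.** The relevant text is the paragraph on multiple comparisons near the end of the Statistical methods section.

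- **Method and family.** "Multiple comparisons within the 2 × 2 factorial framework will be controlled via Bonferroni correction applied within each outcome domain". The domains are listed as "text-based prediction, acoustic baseline, fusion". Bonferroni is the only method named.
- **Fixed effects.** "We will test all fixed effects (model size main effect, temperature main effect, Model Size × Temperature interaction") "at *α* = 0.05 (two-tailed"). No divisor is given.
- **Cell comparisons.** The "comparisons between specific factorial cells (e.g., testing whether GPT-OSS-120B at temperature 0.8 outperforms GPT-OSS-20B at temperature 0.1) will be pre-specified". The sentence adds that they will be corrected, but names neither a method nor a number of comparisons.
- **Intervals.** Tier 1: "Effect sizes will be reported as odds ratios with 95% confidence intervals". Tier 2 promises partial eta-squared "effect sizes with 95% confidence intervals for each factorial term". Neither place mentions a multiplicity adjustment of the intervals.
- **Use of the interaction test.** Tier 2 says that a significant interaction would call for tuning by model, and that its absence would favour one recommendation for both model sizes.

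**The concern.** Single-step Bonferroni compares every p-value in a family of m tests with 0.05/m. Holm compares the smallest p-value with 0.05/m, the next with 0.05/(m − 1), and so on up to 0.05, and stops at the first failure. Holm makes no assumption about dependence that Bonferroni avoids, and it gives the same family-wise guarantee. Because no Holm threshold is below 0.05/m, it cannot lose a rejection that Bonferroni makes.

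At stake is the chance of detecting the second and third real effects in a family. The interaction is the term for which this matters most, because it is the one whose non-significance the plan turns into a deployment message. If size and temperature both have clear effects, Bonferroni still tests the interaction at 0.05/3, although two of the three hypotheses have already been rejected.

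**Working it through.** **1. The plan's own power figure.** The Sample size section powers one two-tailed exact test with null proportion 0.50, effect 0.11 (so 0.61 under the alternative), N = 162 and critical values 68 and 94. The exact binomial calculation gives alpha 0.04917 and power 0.80468, as printed. That calculation contains no multiplicity adjustment, so N does not depend on the choice between Bonferroni and Holm. It also says nothing about power for the factorial tests, so the power below is an assumption.

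**2. Inputs.**
- From the plan: three factorial terms (size, temperature, interaction), two-sided tests, 0.05 taken as the family level.
- Assumed: independent z-tests, with each real effect having 80% power at unadjusted 0.05, so mean z = 1.960 + 0.842 = 2.802.

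**3. Thresholds for m = 3.**
- Bonferroni: 0.05/3 = 0.0167 for every test.
- Holm: 0.0167, 0.025 and 0.05, in order of the p-values.

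**4. Chance that one real effect passes each threshold**, Φ(2.802 − critical z):
- A (0.0167, critical z 2.394): Φ(0.408) = 0.658
- B (0.025, critical z 2.241): Φ(0.560) = 0.712
- C (0.05, critical z 1.960): Φ(0.842) = 0.800

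**5. All three effects real.**
- Bonferroni: 0.658 per effect; all three found, 0.658³ = 0.285.
- Holm, at least one rejection: 1 − (1 − A)³ = 0.960, the same as Bonferroni.
- Holm, at least two: [B³ − (B − A)³] + 3(1 − B)[B² − (B − A)²] = 0.361 + 0.435 = 0.797.
- Holm, all three: [B³ − (B − A)³] + 3(C − B)[B² − (B − A)²] = 0.361 + 0.133 = 0.494.
- Holm, average power: (0.960 + 0.797 + 0.494)/3 = 0.750.

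**6. All scenarios.** Enumeration over the same thresholds agrees with a simulation of 400,000 families to within about 0.1 percentage point:

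| Real effects | Average power, Bonferroni | Average power, Holm | At least one rejection, both methods |
|---|---|---|---|
| 1 of 3 | 66% | 66% | 67% |
| 2 of 3 | 66% | 70% | 89% |
| 3 of 3 | 66% | 75% | 96% |

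In the simulation Holm never missed a Bonferroni rejection. With all three nulls true, the family-wise error was 4.9% for both methods. With one or two effects real, Holm's was 4.4% and 3.7%.

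**7. Interaction when both main effects are clear.** If the two main effects are almost certain to be rejected first, Holm tests the interaction at 0.05 (power C = 80%) and Bonferroni at 0.0167 (power A = 66%). The risk of missing a real interaction falls from 34% to 20%. This is the most favourable case for Holm.

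**8. Cell comparisons.** The article gives no number. For illustration, take all six pairs among four cells, correlated as pairwise differences are, with only model size having an effect. Average power is then 56.5% with Bonferroni and 61.4% with Holm; family-wise error is 1.7% and 2.7%.

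**The case against.** The strongest reply is that Bonferroni is a valid method, named in advance, with strong error control, and that no figure in the article depends on it. That is correct, and a reader should not infer that the planned inference is invalid. The point is only that another procedure with the same guarantee does at least as well.

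Four stronger readings are tempting, and the article does not support them.

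- **That Bonferroni is fixed for every test.** The cell comparisons "will be pre-specified and corrected for multiple comparisons", but that sentence names no method. For the fixed effects, 0.05 appears without a divisor. It may be the family level before division, as the preceding sentence suggests, or the level of each test. On the second reading nothing is lost on those three terms. In the acoustic baseline the Tier 1 predictors are acoustic features, so there are no size or temperature terms to correct.
- **That power is given away for nothing.** Bonferroni has simple matching simultaneous intervals and Holm does not. The plan reports an interval for each factorial term without saying whether it is adjusted. If adjusted intervals are intended, that is a good reason to keep Bonferroni.
- **That the gain is large in general.** It is near zero with one real effect and nil for the chance of any rejection. A figure for six independent, all-real cell comparisons (56.5% against 68.3%) does not fit the design: six differences among four cells are linearly dependent, and only specific cells are to be compared. The 162 interviews do not settle factorial power either, since all four conditions are run on the same sessions.
- **That any missed effect is read as support for one recommendation.** Tier 2 says this only of the interaction. Reading non-significance as support is a separate weakness that Holm does not cure.

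What stands is the dominance of Holm over Bonferroni in every family that is corrected.

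**Conclusion.** The point holds as a cheap improvement. With three tests corrected as a family, the gain in average power runs from almost nothing to about 9 percentage points. For the interaction it can reach about 14 points (80% − 66%) if both main effects are clear. These sizes rest on the assumed 80% unadjusted power per real effect and on independent tests. The direction does not: Holm keeps the family-wise guarantee and rejects at least as much under any dependence. The point covers the text and fusion factorial terms only if 0.05 is a family level, and it covers the cell comparisons once their family is defined.

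**What to change.** In the multiple-comparisons paragraph, replace Bonferroni by Holm step-down for each family that is corrected: the factorial terms in the text domain, those in the fusion domain, and the pre-specified cell comparisons, where the method should be named. In the same edit, say whether 0.05 for the three fixed effects is the family level or the level of each test, since that decides whether the change affects those terms.

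The cost is a few words before the analysis. The sample size and the data collection do not change. The one drawback is the lack of simple matching simultaneous intervals. If the study team wants adjusted intervals, it can keep Bonferroni and give that as the reason. If not, it should describe the 95% intervals as unadjusted, so that readers do not expect them to agree with the Holm decisions.
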